## Abstract

**Background:**

Open surgical repair (OSR) for thoracoabdominal aortic aneurysms (TAA) is associated with a high pulmonary and renal morbidity rate. Ischemic preconditioning (IPC) is a mechanism of protection against the deleterious effects of ischemia-reperfusion. To our knowledge IPC has never been tested during OSR for TAA.

**Methods:**

The primary objective of the study is to evaluate the efficacy of IPC during OSR for TAA with respect to acute kidney injury (AKI) according to KDIGO and pneumonia/prolonged ventilation-time during the first 8 postoperative days. The secondary objectives are to compare both arms with respect to cardiac complications within 48 h, renal and pulmonary complications within 21 days and mortality at 60 days.

To assess the efficacy of IPC with respect to pulmonary and renal morbidity, a cox model for competing risks will be used. Assuming that the event occurs among 36% of the patients when no IPC is performed, the allocation of 55 patients to each arm should allow detecting a hazard ratio of at least 2.75 with a power of 80% when admitting 5% for an error of first kind. This means that 110 patients, enrolled in this multicenter study, may be randomised within 36 months of the first randomization.

Randomization will be performed to allocate patients either to surgery with preconditioning before aortic cross clamping (Arm 1) or to surgery without preconditioning before aortic cross clamping (Arm 2).

Randomization takes place during the intervention after intravenous injection of heparin, or after the start of femoral assistance. The procedure for IPC will be a supra-visceral thoracic aortic cross clamping for 5 min followed by an unclamping period of 5 min. This procedure will be repeated twice before starting thoracic aortic cross clamping needed to perform surgery.

**Conclusions:**

Our hypothesis is that ischemic preconditioning could reduce clinical morbidity and the incidence of lung damage associated with supra-visceral aortic clamping.

**Trial registration:**

EPICATAStudy registered in ClinicalTrial.gov / number: NCT03718312 on Oct.24.2018 URL number

## Background

Mortality rate after OSR for TAA is estimated between 4 and 15% [1, 2]. Pulmonary and renal complications can reach up to 50% and more [3, 4]. Compared to OSR for infrarenal abdominal aortic aneurysm (AAA), TAA requires repair of the visceral arteries with a supravisceral aortic cross-clamping often greater than 30 min. Following OSR for TAA, Serious lung damage reached 60% in large series [3, 5] and 40 to 50% in recent publications [6]. The hypothesis of a causal link between visceral ischemia and the occurrence of organ failure and particularly lung damage is the main focus of this study. Mesenteric ischemia reperfusion caused by aortic cross clamping above the celiac trunk and the superior mesenteric artery is involved in the onset of a systemic inflammatory response (SIRS) leading to multiple organ failure (MOF) [7–10]. Interestingly, distal perfusion of the aorta by a shunt reduces the onset of paraplegia, but increases the production of cytokines and complications associated with the inflammatory response [11, 12].

The main actors of the inflammatory response to ischemia-reperfusion are free radicals’ oxygen, polymorphonuclear neutrophil cells (PMN) and cytokines, all at the origin of the deleterious complications [13–15]. In particular, activity of neutrophils could be a key factor in remote lung injury [16, 17].

Beside remote lung injury, renal damage can be mainly attributed to direct effect of cross aortic clamping during TAA. Severe acute renal failure reaches 25% with dialysis required in 17% of patients [6] with an increased risk of death [18]. Wynn et al. reported that renal failure as defined in the RIFLE classification [19] was not associated with increased mortality [20]. According to Tshomba et al. [21] acute renal failure is often temporary. But even temporary, it is possible that acute renal failure observed in this context may later favour the onset of chronic renal failure [22].

IPC applied to OSR for AAA was reported to reduce myocardial and renal damage [23]. But this result has been debated and other studies have reported negative results with IPC during AAA OSR [24] or peripheral vascular surgery [25]. IPC has been shown to improve lung function measured by blood gases and mesenteric aggression measured by lactate blood level [26]. Finally, a recent meta-analysis of 9 randomized trials, focused on the effects of remote IPC in patients operated for AAA, through an open or an endovascular approach, failed to report any beneficial effect on mortality, myocardial ischemia and renal impairment [27]. But these series were carried out during OSR of infrarenal AAA where the visceral arteries were not involved in aortic reconstruction and by that ischemia reperfusion damage [24, 25]. In these conditions, the protective effects of IPC appear difficult to evaluate [27–29]. In the same way, the CRIPES studying EVAR, which required no aortic clamping, did not show any protective effect of IPC on myocardial function [30]. On the contrary, a recent meta-analysis showed that IPC performed by clamping the thoracic aorta while performing coronary bypass, reduced the duration of postoperative artificial ventilation and myocardial ischemia [31].

### Rationale of the study

Our hypothesis is the existence of a causal relationship between visceral ischemia and remote organ failure. Visceral aortic cross clamping causes mesenteric and renal cells ischemia reperfusion injury leading to an intense and systemic inflammatory activity which could affect remote organs.

IPC may be a useful tool for endogenous protection against the deleterious effects of ischemia-reperfusion has been already demonstrated in myocardial ischemia [32], liver and kidney ischemia [33], but IPC for direct OSR of TAA requiring supravisceral aortic cross clamping has never been tested.

## Methods/design

### Trial objective

The primary objective of the study is to evaluate the efficacy of IPC applied directly to the supravisceral aorta during OSR for TAA with respect to acute kidney injury (AKI) according to KDIGO and pneumonia/prolonged ventilation-time during the 8-day postoperative period.

The secondary objectives are to compare both arms with respect to cardiac complications within 48 h, renal and pulmonary complications within 21 days and mortality at 60 days.

### Trial design

EPICATA is a randomized, open, multicentric national French study, the essential aspects of which have been summarized on a flowchart (Fig. 1).

**Fig. 1 Fig1:**
[figure not shown]
Study protocol flow chart

### Primay endpoint

The primary endpoint is the occurrence of a first pulmonary or renal complication during the 8-day postoperative period.

Pulmonary complications are defined as:
The necessity of prolonged artificial ventilation, i.e. no extubation before the 48-h following the surgeryThe need for a new ventilation (invasive or noninvasive) within 48-h following initial extubationThe occurrence of a moderate or severe acute respiratory failure, according to the Berlin definition [34].

Renal complication is defined as the occurrence of an acute kidney failure according to the RIFLE classification [19], as “injury”, “failure” or “loss” during the first postoperative week.

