**Arterial blood samples: lactates and blood gas at H1, H3 and daily (D1 to D8)**	
**Venous blood samples: serum creatinine at H3 and daily from D1 to D8**	
**Venous blood samples: Troponin on D1, D2**	
**Hourly urine volume output**	
**Duration of hemodialysis, if any**	
**Length of stay in intensive care unit**	

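### The renal endpoint is scored by RIFLE class alone and does not count dialysis, so a few patients dialysed early could be scored event-free; the objective names KDIGO instead.

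*Protocol article*

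**What the plan says.** The primary endpoint is "the occurrence of a first pulmonary or renal complication during the 8-day postoperative period". For its renal half, the primary endpoint section says: "Renal complication is defined as the occurrence of an acute kidney failure according to the RIFLE classification". The qualifying classes are injury, failure or loss, "during the first postoperative week". The Secondary endpoints section uses RIFLE again for renal failure over 21 days. Neither section mentions dialysis.

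The Trial objective section, like the Abstract, refers to "acute kidney injury (AKI) according to KDIGO". The objective and the endpoints therefore name different classifications, and the article reproduces the criteria of neither.

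Table 2 lists the renal data: "serum creatinine at H3 and daily from D1 to D8", hourly urine volume with no stated last day, and "Duration of hemodialysis, if any". No listed endpoint uses the dialysis item. The Background reports from the literature: "Severe acute renal failure reaches 25% with dialysis required in 17% of patients".

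**The concern.** Serum creatinine measured after dialysis has started reflects the dialysis as well as the kidney. If an event can be reached only through a RIFLE class, a patient who starts dialysis before meeting one may never meet one afterwards. The endpoint would then record no renal complication in a patient whose kidneys were being replaced by a machine. The trial collects the information needed to prevent this and does not use it.

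The trial is open (Trial design), and starting dialysis is a decision of clinicians who may know the allocation. Any such loss could therefore differ between arms. Only about 28 primary events are expected, so a few misclassified patients are noticeable. The planned Cox model for competing risks also needs event times, and for dialysis Table 2 names only a duration.

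**Working it through.** **Who is exposed.** The article does not reproduce the RIFLE criteria. I assume that the classes are read from the creatinine and urine output listed in Table 2, and that starting dialysis does not by itself confer a class. A patient is then missed only if all of these hold:

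1. Dialysis starts before any qualifying class is met. The endpoint is a first occurrence, so an event already met stays counted.
2. Urine output stays high enough not to qualify. It is recorded hourly.
3. None of the three pulmonary criteria is met in the window.

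This group is narrow: early, non-oliguric dialysis without a pulmonary event. For the 21-day endpoint it is wider, because no creatinine is scheduled after day 8.

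**Inputs.** From Number of patients to be enrolled: 55 per arm, control risk 36%, preconditioning risk 15%, hazard ratio 2.75. From the Background: dialysis in 17%. Assumed: the 17% applies to controls within the window, these patients lie within the planned 36%, and a share f of them is missed, with f from 10% to 30%. The documents give no value for f.

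**The plan's own hazard ratio.** ln(1 − 0.36) / ln(1 − 0.15) = 2.746, which reproduces 2.75. Expected events are 55 × 0.36 = 19.8 in controls and 55 × 0.15 = 8.25 with preconditioning, 28.05 in all.

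**Control events lost.** 0.17 × 55 = 9.35 dialysed controls.
- f = 10%: 0.94 events lost; control risk 0.36 − 0.017 = 34.3%.
- f = 30%: 2.81 events lost; control risk 0.36 − 0.051 = 30.9%.

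**Proportional loss in both arms.** Dialysis in the preconditioning arm is scaled by 15/36, giving 9.35 × 15/36 = 3.9 patients. Power is Φ(½√E × ln HR − 1.96), with E the number of events.

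| f | Control risk | Preconditioning risk | Events | Hazard ratio | Power |
|---|---|---|---|---|---|
| 0 | 36.0% | 15.0% | 28.05 | 2.75 | 76.3% |
| 10% | 34.3% | 14.3% | 26.7 | 2.72 | 73.6% |
| 25% | 31.8% | 13.2% | 24.7 | 2.69 | 69.2% |
| 30% | 30.9% | 12.9% | 24.1 | 2.68 | 67.7% |

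Between 1.3 and 4.0 of 28 events are lost, and the hazard ratio is almost unchanged. The first row gives 76.3% rather than the stated 80%. That is a separate sample-size matter; here only the differences between rows count.

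**Bounding case.** If every missed patient were a control, the hazard ratio would be ln(1 − 0.343) / ln(0.85) = 2.58 at f = 10% and ln(1 − 0.309) / ln(0.85) = 2.27 at f = 30%. Nothing in the documents makes this one-sided loss likely.

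**The case against.** The case against is strong on size. A reader might infer that dialysis erases primary events, or that the sickest kidneys go uncounted. The documents do not support either. A first event met before dialysis is not undone by a later fall in creatinine, and hourly urine output should identify oliguric patients. Those who escape both are not evidently the sickest. The Background reports dialysis alongside severe renal failure, which suggests that many dialysed patients would already have an event.

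The 17% is a published figure without a time window, not a forecast for this trial's first 8 days. The article nowhere describes dialysis as a permitted rescue treatment; it only records its duration. The missed share is assumed. If the 36% was itself counted without patients dialysed below the threshold, nothing should be subtracted from it. A reader might also take the fall to 2.27 as the expected bias, but it needs every miss to fall in one arm.

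Two further objections carry weight. Making dialysis an event brings a discretionary decision into the primary outcome of an open trial. And a condensed article may leave the reading of creatinine on dialysis, and the date fields, to the full protocol or analysis plan.

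What remains is that the article does give an operative definition of the renal event. It leaves dialysis out in both endpoint sections and conflicts with the objective's classification. The KDIGO wording makes the definition contradictory; it does not close the gap.

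**Conclusion.** The point holds in limited form. The renal event is defined by RIFLE class in the endpoints and by KDIGO in the objective, and dialysis, though recorded, counts in neither endpoint. A small number of patients could be scored event-free as a result, and the 21-day endpoint is more exposed than the primary one.

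Under the stated assumptions, the loss is about 1–3 of 20 control events, or 1–4 of 28 in both arms together. Power falls by roughly 3 to 9 percentage points across the assumed range, and the hazard ratio hardly moves. Bias between arms is possible in an open trial but is not demonstrated. The conclusion rests on RIFLE being read from creatinine and urine output alone, on applying the 17% to the window, and on the assumed missed share. It is worth correcting because the correction is cheap, not because the effect is shown to be large.

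**What to change.** 1. Name one renal classification, with its qualifying classes, in the Abstract, the Trial objective and both endpoint sections. State one renal window for the primary endpoint: the article gives both 8 days and the first postoperative week.
2. In both endpoint sections, count any new postoperative renal replacement therapy within the window as a renal event, dated at its start.
3. State that creatinine values obtained after dialysis has started are not used to rule out a renal event.
4. Record the dialysis start date beside the duration already in Table 2.
5. Report the renal component without the dialysis criterion as a sensitivity analysis, because starting dialysis is a clinician's decision in an open trial.

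The cost is a few sentences, one date field and one extra analysis. The downside is some subjectivity in the added event, which item 5 makes visible. The change concerns outcome scoring only and has no bearing on when a patient is dialysed.

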### Secondary endpoints

The secondary endpoints are:
Need for new ventilation (invasive or noninvasive) 48 h after the arrest of initial ventilation, during a 21-day postoperative period.Renal failure occurring during a 21-day postoperative period according to the RIFLE classificationCardiac morbidity: daily serum troponin > 1.5 normal level (specific in each center) within the 48-h postoperative period.Cellular and tissue visceral impairment: daily serum D-lactate during the first 8-day postoperative period.Mortality at 60 days

This study is randomized in two arms on the day of surgery by drawing lots
Arm 1: patients with aortic clamping with preconditioningArm 2: patients with aortic clamping without preconditioning

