### Number of patients to be enrolled

The sample size is calculated taking into account an estimated risk of pulmonary and renal complications around 36% following OSR for TAAA in patients operated without PCI [6] and a postoperative mortality around 1% of the patients before the 8th day (observed in the selected centres). With the hypothesis of a corresponding risk in the PCI group around 15%, the randomization of 110 patients, with an allocation ratio of one to one, will detect a Hazard Ratio ≥ 2.75 between both arms with a power of 80% and an alpha risk of 5%.

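### The primary outcome is stated in two partly overlapping ways (KDIGO with pneumonia; RIFLE with re-ventilation and Berlin criteria), and the renal window conflicts with the composite window

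*Protocol article*

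**What the plan says.** The Trial objective section of the protocol article sets the efficacy question on "acute kidney injury (AKI) according to KDIGO and pneumonia/prolonged ventilation-time during the 8-day postoperative period". The Abstract (Methods) has the same content: "acute kidney injury (AKI) according to KDIGO and pneumonia/prolonged ventilation-time during the first 8 postoperative days". Neither gives a KDIGO stage or a threshold for prolonged ventilation.

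The Primary endpoint section begins: "The primary endpoint is the occurrence of a first pulmonary or renal complication during the 8-day postoperative period". It then lists three pulmonary criteria: no extubation before 48 hours after surgery, new ventilation within 48 hours of the first extubation, and moderate or severe acute respiratory failure by the Berlin definition. On the renal side it says "Renal complication is defined as the occurrence of an acute kidney failure according to the RIFLE classification", restricts this to the categories injury, failure or loss, and sets the window as "during the first postoperative week".

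The Secondary endpoints section also uses RIFLE for renal failure, over 21 days. Table 2 lists ventilation hours, the Berlin data, urine output and "serum creatinine at H3 and daily from D1 to D8". The sample-size section (Number of patients to be enrolled) plans on "an estimated risk of pulmonary and renal complications around 36" percent in controls and about 15% with preconditioning. The Trial design section describes the study as open.

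**The concern.** The primary endpoint decides which patients are events, and this article gives two rules for it. The endpoint section names neither KDIGO nor pneumonia. The Abstract and objective name none of RIFLE, re-ventilation or the Berlin definition. Nothing states that one text is shorthand for the other or that one takes precedence.

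Two things are at stake. First, the event count, the hazard ratio and the test result can depend on which text is applied. Second, arm is known in an open trial, so a definition still unsettled at analysis leaves a choice that could be made, or appear to have been made, with the results in view.

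**Working it through.** **Side by side**

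| Element | Abstract and Trial objective | Primary endpoint section |
|---|---|---|
| Renal classification | KDIGO | RIFLE |
| Renal threshold | none stated | injury, failure or loss |
| Renal window | 8 days | first week (composite: 8 days) |
| Prolonged ventilation | yes, no threshold | yes, not extubated by 48 h |
| Pneumonia | yes | no |
| Re-ventilation within 48 h | no | yes |
| Moderate or severe Berlin failure | no | yes |

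**Patients whose status changes** (each with no other qualifying event)

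- Pneumonia only: an event under the objective, not under the endpoint section.
- Early re-ventilation only, or Berlin failure only: an event under the endpoint section, not under the objective.
- Kidney injury below RIFLE injury: excluded by the endpoint section; the objective sets no floor.
- Qualifying renal event first reached on day 8: inside the composite window, outside the renal window. Creatinine is taken on day 8, so such a case would be seen.

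**The planning figures**

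Inputs from the sample-size section: 36% against 15%, 110 patients at 1:1, 80% power, alpha 5% (two-sided per Statistical methods).

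1. Hazard ratio: ln(1 − 0.36)/ln(1 − 0.15) = 2.746, which reproduces the stated 2.75.
2. Expected events: 55 × (0.36 + 0.15) = 28.05.
3. Schoenfeld power: Φ(√28.05/2 × ln 2.75 − 1.96) = 0.764.

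The stated 80% is therefore not reproduced two-sided. By this formula 31 events are needed, and 31/0.255 = 122 patients. That is a separate matter. Here, 76% is the baseline for the comparisons below.

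**Which definition the 36% belongs to**

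This cannot be read from the article. The Background cites the same source as the 36% for serious lung damage of 40 to 50% and severe acute renal failure of 25%. A composite rate below that lung rate is not visibly tied to either text.

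**Illustrations (the added events are assumptions, not in the documents)**

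Let a second definition add events in a fraction q of patients, independently of those already counted, in both arms and unaffected by preconditioning. Risks become 1 − 0.64(1 − q) and 1 − 0.85(1 − q).

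| q | Risks | HR | Events | Power |
|---|---|---|---|---|
| 0 | 36% / 15% | 2.75 | 28.0 | 76% |
| 5% | 39% / 19% | 2.33 | 32.1 | 67% |
| 10% | 42% / 24% | 2.06 | 36.2 | 58% |
| 20% | 49% / 32% | 1.74 | 44.4 | 45% |

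If the 20 points are instead added with no overlap, risks are 56% and 35%, HR = ln(0.44)/ln(0.65) = 1.91, events = 50.05, and power is 63%.

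If preconditioning acts on the added events equally (HR stays 2.75), power rises. With control risk 48.8% (q = 20%, independent), the other arm has 1 − 0.512^(1/2.75) = 21.6%, events = 38.7, power 88%. With control risk 56% (no overlap), the other arm has 1 − 0.44^(1/2.75) = 25.8%, events = 45.0, power 92%.

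**The case against.** The two texts are not of equal standing. The objective is a summary without stage or threshold; the endpoint section is the only operational text. The secondary renal endpoint also uses RIFLE, and the Table 2 data suit the endpoint section. The likeliest reading is loose or outdated wording in the Abstract and objective. This stands as an argument for which text to keep. It does not remove the contradiction, because the article never says which governs. A separate analysis plan could elaborate one version but could not make both true.

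A reader might infer four stronger points that the documents do not support:

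- **That the definitions are wholly incompatible.** They share prolonged ventilation and overlap in part.
- **That the secondary re-ventilation rule is an error.** The primary endpoint counts re-ventilation within 48 hours of extubation; the secondary one is "Need for new ventilation (invasive or noninvasive) 48 h after the arrest of initial ventilation, during a 21-day postoperative period". These may be an intended early and late pair, and need not match.
- **That the planning rates can fit only one definition.** The source of the 36% is not at hand, so this cannot be shown.
- **That the trial demonstrably loses power.** The added events are assumed, and even the direction of the effect is unknown.

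The absence of pneumonia from Table 2 may reflect condensation for a journal. It supports keeping the endpoint section but is not a defect in itself. The week against 8 days is a difference of one day, and nothing shows that it would alter a result. It is still a contradiction inside the primary endpoint and is best removed in the same edit.

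**Conclusion.** The point holds as an internal inconsistency in the primary outcome. The renal classification, the renal threshold and part of the pulmonary component differ between the Abstract and objective on one side and the endpoint section on the other, and the endpoint section carries two renal windows. Because this is the primary endpoint of an open trial, it should be settled before analysis.

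The number of patients who would be reclassified cannot be computed from the documents. The power figures only show that the choice of definition could matter: from a baseline of about 76%, 45% to 67% if 5% to 20% of patients have added events that preconditioning does not affect, and above 90% if 20 points are added without overlap and preconditioning affects them equally. They assume proportional hazards and leave out the 1% early mortality, which changes the baseline by less than one point.

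**What to change.** State one primary endpoint definition in the Abstract, the Trial objective and the Primary endpoint section. The simplest choice is the operational text already in the endpoint section: RIFLE injury, failure or loss; no extubation by 48 hours; re-ventilation within 48 hours of extubation; moderate or severe Berlin respiratory failure. KDIGO and pneumonia would then come out of the primary objective.

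Use one window for the renal and pulmonary components. Eight days fits the composite and the creatinine schedule. State in the sample-size section that the 36% and 15% refer to this definition.

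If KDIGO is kept instead, name the minimum stage and re-derive both rates and the sample size. The secondary re-ventilation endpoint can stay as it is.

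The cost is a wording amendment before analysis. The data listed in Table 2 already support the endpoint-section definition, so no new collection is needed for that choice.
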